### Study design

2.1

This study is a prospective, single-center, randomized controlled clinical trial. Patients with CTO who underwent PCI in the cardiology department of our hospital. Using a computer-generated block randomization sequence (block size = 4), participants were allocated in a 1:1:1:1 ratio to one of four parallel groups: the SBP group, the exercise rehabilitation group, the combined SBP and exercise rehabilitation group, and the control group. Allocation concealment was ensured by a central randomisation module embedded in the Hospital Information System (HIS); the treatment assignment was automatically released only after the participant had been registered and baseline data entry was completed. Figure 1 shows the details of the study process. This study will strictly adhere to the Standard Protocol Items: Recommendations for Interventional Trials (SPIRIT) reporting standard (20).

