#### Exclusion criteria

2.2.2

Patients with cardiovascular and cerebrovascular accidents (such as acute myocardial infarction, cerebral hemorrhage, and cerebral embolism) within the past 6 months.

Patients with severe heart failure symptoms or left ventricular ejection fraction <40%.

Patients with severe renal insufficiency requiring dialysis.

Patients with bleeding tendency, a history of active peptic ulcer, cerebral hemorrhage or subarachnoid hemorrhage, a history of stroke within the past 6 months, and contraindications to antiplatelet and anticoagulant therapy.

Patients with sick sinus syndrome, second-degree type I or third-degree atrioventricular block.

Unstable angina patients with resting angina attacks within 48 h.

Patients with a life expectancy <12 months.

Patients with significantly limited exercise capacity.

Patients with poor compliance who cannot complete the study as required.

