### Intervention measures

2.3

As an interventional trial, blinding of participants, treating physicians, and researchers directly involved in intervention implementation was not feasible due to the specific nature of the interventions (including oral SBP and exercise rehabilitation training), whose distinct characteristics would render blinding impractical. Importantly, outcome assessors responsible for data collection and statisticians conducting post-data-collection analyses remained blinded to group allocation throughout the study.

If a participant learns their group assignment during rehabilitation exercises, they will be assessed. If this knowledge could influence their behavior, they may be excluded from the study. Additionally, other participants will be monitored for information leaks. If others are affected, measures like re-evaluating data validity or exclusion from the study will be taken.

Tables 1–6 show the details content of the pre-exercise assessment, the three-phase exercise prescription, the exercise intensity grading, the type of exercise, the remote monitoring, and the outpatient period training program, respectively. The principles of full-cycle rehabilitation are shown in Figure 2. The schedule in this study is shown in Figure 3.

**Table 1 tab1:** Pre-exercise assessment.

Component	Detailed design
Cardiopulmonary function	CPET to measure VO_2_ peak and anaerobic threshold (AT)
Exercise risk stratification	AACVPR risk stratification criteria (incorporating LVEF, arrhythmia history)
Muscle function evaluation	30-s chair stand test, grip strength measurement
Psychological assessment	Hospital anxiety and depression scale (HADS)
Vascular evaluation	Coronary flow reserve (CFR), index of microcirculatory resistance (IMR, optional)

CPET, cardiopulmonary exercise test; AACVPR, American Association of Cardiovascular and Pulmonary Rehabilitation, LVEF, left ventricular ejection fraction.

**Table 2 tab2:** Three-phase exercise prescription.

Phase	Timeframe	Primary goals	Monitoring	Termination Criteria
Phase I	(Inpatient) 2–7 days post-PCI	Prevent deconditioning	Daily assessment	Chest pain > CCS Class II, SpO2 < 90%
Phase II	(Outpatient) 1–6 months post-discharge	Improve aerobic capacity	Weekly onsite + remote	ST depression ≥2 mm, SBP drop >10 mmHg
Phase III	(Home-based) 7–12 months	Long-term maintenance	Monthly follow-up	New-onset VT/AF

CCS, Canadian Cardiovascular Society, VT’AF, ventricular tachycardia/atrial fibrillation.

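### The plan allows randomised participants to be excluded for knowing their own allocation, although participants are unblinded by design, which builds in a risk of selection bias of unknown size and direction

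*Protocol article*

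**What the plan says.** All the relevant text on blinding is in the protocol article, Section 2.3 (Intervention measures).

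- The first paragraph says that "blinding of participants, treating physicians, and researchers directly involved in intervention implementation was not feasible". The blinding that remains applies to others: "outcome assessors responsible for data collection and statisticians conducting post-data-collection analyses remained blinded to group allocation throughout the study".
- The next paragraph sets the rule. "If a participant learns their group assignment during rehabilitation exercises, they will be assessed". Then: "If this knowledge could influence their behavior, they may be excluded from the study".
- The rule extends to other participants, who are to be watched for leaks. "If others are affected, measures like re-evaluating data validity or exclusion from the study will be taken".

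Section 2.1 (Study design) fixes the timing of allocation: "the treatment assignment was automatically released only after the participant had been registered and baseline data entry was completed". Sections 2.3.1 to 2.3.4 describe the four arms: Shexiang Baoxin pill, exercise rehabilitation, both, and routine post-PCI care. No placebo or sham is described.

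**The concern.** The two paragraphs of Section 2.3 do not fit together. A trial that accepts that participants know their treatment cannot also treat that knowledge as a reason to remove them.

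The consequence matters more than the inconsistency. Randomisation makes the arms comparable only if the participants who were randomised are the ones compared. A rule that lets staff take people out afterwards, on a judgement about their behaviour, can make the remaining participants differ between arms. Behaviour in a rehabilitation trial is plausibly linked to adherence and prognosis, and so to the 1-year perfusion measures (MBF and SDS), the Seattle Angina Questionnaire and angina incidence. Blinded assessors and statisticians do not help here, because the problem lies in who remains and not in how they are measured. A larger sample does not remove it either.

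**Working it through.** **Reading the text**

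1. *Is the trigger an unusual event?* No. Participants swallow a pill or do not, and attend exercise sessions or do not, with nothing to mask either. Table 8 adds education before the pill is started and daily medication reminders. Section 2.3.2 adds nurse-guided exercise and weekly calls. Section 2.4 says that patients are informed of the trial before consent. Anyone in a rehabilitation session knows that they have been given exercise.
2. *Is the second condition a real filter?* Hardly. It asks whether the knowledge could influence behaviour. In an exercise trial, changing behaviour is the purpose. No threshold, criterion or responsible assessor is given.
3. *Is the exclusion after randomisation?* Yes. Section 2.1 releases the assignment after registration and baseline entry, and learning it during rehabilitation comes later still.
4. *Is it tied to arm?* The primary trigger is. Protocol exercise is described for the exercise and combined arms only (Sections 2.3.2 and 2.3.3), which is two of four. The leak clause names no arm and can reach all four.

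**Size, as illustration only**

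Section 2.9 gives no sample size, SD or effect size, because these await pilot studies. There is therefore no figure in the plan to reproduce, and every input below except the 0.05 significance level is an assumption.

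*Model A.* Suppose the lowest share q of an exercise arm is removed on a normally distributed trait that has correlation r with the outcome. The mean of those retained shifts by r × φ(z_q) / (1 − q) SD.

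| q | φ(z_q)/(1 − q) | r = 0.3 | r = 0.5 | r = 0 |
|---|---|---|---|---|
| 10% | 0.1755/0.9 = 0.195 | 0.058 | 0.097 | 0 |
| 20% | 0.2800/0.8 = 0.350 | 0.105 | 0.175 | 0 |

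If the rule removed the most favourable participants instead, the sign would reverse.

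*Model B.* Suppose retained and excluded participants differ by d SD. The retained mean then shifts by q × d. With q = 5–20% and d = 0.5–1.0, the shift runs from 0.05 × 0.5 = 0.025 SD to 0.20 × 1.0 = 0.20 SD. With no true treatment effect, exclusions in the two exercise arms only, and 30–100 participants per arm before exclusion, the nominal 0.05 two-sided error becomes:

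- 0.051 to 0.27 for a comparison of an exercise arm with a non-exercise arm;
- 0.051 to 0.32 for the four-arm ANOVA.

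The lower ends are 30 per arm, q = 5%, d = 0.5. The upper ends are 100 per arm, q = 20%, d = 1.0. With d = 0 the error stays at 0.05.

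*Without the rule.* If nobody is excluded on this ground and everyone is analysed as randomised, the rule contributes no bias at any sample size.

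**The case against.** The strongest reply is that the rule is conditional. A participant is first assessed, and may then be excluded. For those touched by leaks, the text offers a check on data validity as an alternative to exclusion. The rule might never be used, and its likely aim, preventing contamination between arms, is legitimate. The analysis set and a contamination sensitivity analysis also commonly belong in a statistical analysis plan, which is not shown.

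Much of this stands, and it limits what can be said. A reader might go further in five ways that the document does not support:

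- *That the arms are already thinned and the comparison already biased.* The text permits exclusion. It gives no frequency and reports none. That every exercise participant meets the trigger means only that each could be assessed, not that each would be excluded.
- *That only the exercise arms can lose participants.* The primary trigger is specific to those arms, but the leak clause is not.
- *That the entry criterion on compliance does the same harm.* "Patients with poor compliance who cannot complete the study as required" stands in the list of exclusion criteria and reads as an ordinary screening judgement. Nothing says that it is applied after allocation. Section 2.5.1 and Table 8 answer later non-compliance with contact and support, not removal.
- *That these losses fall outside the 20% dropout allowance.* Section 2.9 does not define dropout closely enough to say. The power cost is small in any case. Removing a further 5%, 10% or 20% from one arm takes a 90% pairwise comparison to Φ(3.2415 × √(2/(1 + 1/(1 − q))) − 1.960), about 89%, 88% or 86%.
- *That the decision is taken by unblinded staff.* The text does not say who decides. It supports only the statement that no assessor and no criterion are named.

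What the reply does not answer is the rule itself. The fault is not an unnamed analysis set but a stated provision for removing people from the study. If their 1-year outcomes are then not collected, no analysis set defined elsewhere can recover them.

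**Conclusion.** The point holds as a defect in the stated rule. Section 2.3 contradicts itself on participant knowledge of allocation. It allows discretionary exclusion after randomisation without an objective criterion, on a trigger that is met by design and whose primary form exists in only two of four arms. Nothing elsewhere in the article cancels it.

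The consequence is a risk of selection bias of unknown size and direction. The 0.06–0.18 SD shift shows what could happen under assumed exclusion of 10–20% and an assumed correlation of 0.3–0.5. It does not estimate what will happen, and it is zero if the reason for removal is unrelated to outcome. The rule should be removed before it can be applied, because the damage cannot be undone once outcomes have gone uncollected.

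**What to change.** In Section 2.3:

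1. Delete the provisions for excluding participants who learn their assignment or who are affected by information leaks.
2. State that all randomised participants are followed to 1 year and analysed in the arm to which they were assigned.
3. State that cross-arm contamination, such as a participant taking up a component of another arm, is recorded as a protocol deviation and examined only in a sensitivity analysis. The details can sit in the statistical analysis plan.
4. Limit unblinding reports to the outcome assessors and statisticians, who are the people meant to be blinded.

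The cost is protocol wording only, with no extra patients or procedures.

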**Figure 2 fig2:**
[figure not shown]
The principles of full-cycle rehabilitation.

**Figure 3 fig3:**
[figure not shown]
Standard protocol process, schedule covering enrolment, interventions, and assessments (according to SPIRIT).

#### Shexiang Baoxin pill intervention

2.3.1

Patients in the SBP group will start taking two pills, three times a day orally after surgery for 12 months.

#### Exercise rehabilitation intervention

2.3.2

Patients in the exercise rehabilitation group will undergo a comprehensive assessment before exercise, including general function assessment, exercise risk assessment, exercise tolerance assessment, and psychological assessment. Then, the exercise intensity will be set according to their individual conditions and cardiopulmonary exercise test results. They will be divided into low-intensity, medium-intensity, and high-intensity rehabilitation groups. The exercise program will include aerobic exercise, resistance exercise, and flexibility exercise. During the hospitalization period (acute phase, phase I), the responsible nurse will guide patients to perform rehabilitation exercises. After discharge, patients will receive early outpatient rehabilitation (stable phase, phase II) and maintenance-phase outpatient rehabilitation. The responsible nurse will conduct weekly telephone follow-ups to monitor and guide patients’ exercise implementation.

#### Combined intervention

2.3.3

Patients in the SBP combined with exercise rehabilitation group will receive both SBP treatment and exercise rehabilitation training as described above.

#### Control group

2.3.4

Patients in the control group will receive routine post-PCI treatment.

### Data collection and outcome measures

2.4

Eligible patients will be informed of the trial, agree to participate, and voluntarily sign the informed consent form. At the first visit, clinicians will collect basic clinical data of patients, including gender, age, medical history, and medication history. The next day, special personnel will measure patients’ height, weight, waist circumference, and resting blood pressure, and collect fasting venous blood for biochemical tests. In the data collection process, participants are assigned ID numbers, which are used as their identifiers in the system to safeguard their real identities. The collected information is stored in a highly secure database with strict access control, accessible only to the study leader and statistical experts. This ensures effective protection of participants’ privacy throughout the trial. Details of the outcome measures are shown in Table 7.

**Table 7 tab7:** Details of the outcome measures.

Outcome type	Specific content	Evaluation time	Evaluation method
Primary outcome	Evaluation of coronary microcirculation	Immediately and 1 year after revascularization	Myocardial contrast echocardiography (MCE): MBF; myocardial perfusion imaging (MPI): SDS
Secondary outcomes	Incidence of angina pectoris	1 month, 3 months, 6 months, and 12 months after revascularization	Clinical observation and recording
Secondary outcomes	Incidence of MACE during hospitalization, including all-cause death, recurrent myocardial infarction, and target lesion revascularization	Period of hospitalisation after revascularisation	Clinical observation and recording
Secondary outcomes	Incidence of 1-year MACE, including all-cause death, recurrent myocardial infarction, and target lesion revascularization	1 year after revascularization	Clinical observation and recording
Secondary outcomes	Assessment of quality of life improvement using SAQ	Period of outpatient review after discharge	Scoring with the validated Chinese version of the SAQ
Secondary outcomes	Inflammatory factors, angiogenesis-related factors, exercise-related factors	1 month, 3 months, 6 months, and 12 months after revascularization	Biochemical tests: IL-1, IL-6, and TNF; VEGF, Ang, NO, and eNOS; FSTL1 and FGF 21
Safety outcomes	Monitoring of liver and kidney function, metabolism, and nutrition-related indicators to assess the safety of long-term use of SBP and exercise rehabilitation training	Period of outpatient review after discharge	Biochemical tests: ALT; Scr; ALB; FBG, and HbA1c; TC

MBF, myocardial blood flow; SDS, summed difference score; MACE, major adverse cardiovascular events; SAQ, Seattle angina questionnaire, SBP, Shexiang Baoxin pill, IL-l, interleukin-1, IL-6, Interleukin-6; TNF, tumor necrosis factor; VEGF, vascular endothelial growth factor; Ang, angiopoietin; NO, nitric oxide (NO); eNOS, endothelial nitric oxide synthase, FSTL1, Follistatin-like protein 1; FGF 21, fibroblast growth factor 21; ALT, alanine transaminase; Scr, serum creatinine; ALB, albumin; FBG, fasting blood glucose; HbA1c, glycated hemoglobin A1c; TC, total cholesterol.

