**Methods:**

This prospective, single-center, randomized controlled trial involves CTO-PCI patients divided into four groups: Shexiang Baoxin pill, exercise rehabilitation, combined, and control. The exercise protocol includes pre-assessment, a three-phase prescription, CPET-based intensity grading, various exercise methods, remote monitoring, and quality control. The primary outcome is coronary microcirculation assessed by myocardial contrast echocardiography and stress myocardial perfusion imaging 1-year post-surgery. Secondary outcomes include angina incidence, major adverse cardiovascular events (MACE), quality-of-life improvements, and mechanism-related biological indicators, with safety outcomes monitoring liver and kidney function. Data will be analyzed statistically.

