### Statistical analysis

2.9

In this study, there is currently insufficient reference data based on the primary outcome to support sample size calculations; therefore, pilot studies are being conducted to obtain the key parameters required for the formula:

$$n=\varphi^{2}(\sum S_{i}^{2}/g)/[\sum {\left({\bar{X}}_{i}-\bar{X}\right)}^{2}/(g-1)]$$

(where the formula parameter *g* = 4, representing a total of 4 groups in the study) to estimate the required sample size scientifically and accurately, with the significance level set as two-tailed *α* = 0.05, the statistical power set as 1-*β* = 90% (*β* = 0.1), and after calculating the theoretical sample size for each group using the formula upon completion of the pilot studies, a 20% dropout rate will be considered to adjust the theoretical sample size to obtain the final sample size for each group, with the total sample size of the study being the final sample size of each group multiplied by 4.

Statistical analyses will be conducted using appropriate methodologies based on the data characteristics. Continuous variables will be reported as means ± standard deviations, while categorical variables will be presented as frequencies and percentages. Group differences will be assessed using t-tests, analysis of variance (ANOVA), or chi-square tests, as appropriate. A *p*-value of less than 0.05 will be considered indicative of statistical significance. All statistical analyses will be conducted using software such as SPSSAU.

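### No named test adjusts for the immediate post-PCI MBF and SDS, and the text leaves open whether the 1-year value or the change is compared: a loss of precision, not of validity

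*Protocol article*

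**What the plan says.** **Primary outcome.** Table 7 (Section 2.4) gives the measures as "Myocardial contrast echocardiography (MCE): MBF; myocardial perfusion imaging (MPI): SDS" and their timing as "Immediately and 1 year after revascularization". The abstract describes the primary outcome as "coronary microcirculation assessed by myocardial contrast echocardiography and stress myocardial perfusion imaging 1-year post-surgery", which mentions the later time only.

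**Analysis.** Section 2.9 states: "Group differences will be assessed using t-tests, analysis of variance (ANOVA), or chi-square tests, as appropriate". It names no method that takes a baseline covariate. The sample-size formula in the same section uses group means and group variances for four groups, which is the one-way ANOVA form. It has no term for the correlation between the two measurements. The section also says that pilot studies are still under way to supply the inputs, so no sample size is fixed yet.

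**Quality of life.** Table 7 lists "Assessment of quality of life improvement using SAQ" with timing "Period of outpatient review after discharge". On entry data, Section 2.4 says that "clinicians will collect basic clinical data of patients, including gender, age, medical history, and medication history". Body measurements, blood pressure and fasting blood follow the next day. The SAQ is not named there, nor in the pre-exercise assessment of Table 1, which does name the HADS.

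**The concern.** The trial pays for two MCE and two MPI examinations per patient. The first is a natural covariate for the second, because patients with better perfusion just after PCI are likely to have better perfusion a year later. As worded, the analysis may compare 1-year values and leave the first scan unused, or it may compare raw changes. These two analyses can differ widely in precision, and neither is the most efficient use of the pair. The discussion itself expects that dropout may be high and weaken the study, so precision that costs nothing is worth having.

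For the SAQ, the word improvement implies a starting value. The pill begins after the procedure (Section 2.3.1) and Phase I exercise runs on days 2 to 7 (Table 2). A first SAQ at an outpatient review would therefore be taken on treatment. A pre-treatment SAQ that was not collected cannot be recovered by any later analysis plan.

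**Working it through.** **Inputs.** From the article: four groups allocated 1:1:1:1, two-sided alpha 0.05, power 90%, dropout 20%. Not in the article: effect size, group means, standard deviations, and the correlation ρ between the immediate and 1-year values. There is therefore no stated figure to reproduce. Everything below that depends on ρ or on an effect size is an illustration on assumed values.

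**Step 1: variance factors.** Let σ² be the within-group variance, taken as equal at the two times. Relative to an unadjusted comparison of 1-year values (factor 1):

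- raw change: Var(Y₁ − Y₀) = 2σ²(1 − ρ), so the factor is 2(1 − ρ);
- ANCOVA on Y₀: residual variance σ²(1 − ρ²), so the factor is 1 − ρ².

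| Assumed ρ | Raw change, 2(1 − ρ) | Effect on variance | ANCOVA, 1 − ρ² | Effect on variance |
|---|---|---|---|---|
| 0.2 | 1.60 | +60% | 0.96 | −4% |
| 0.3 | 1.40 | +40% | 0.91 | −9% |
| 0.5 | 1.00 | 0% | 0.75 | −25% |
| 0.7 | 0.60 | −40% | 0.51 | −49% |
| 0.8 | 0.40 | −60% | 0.36 | −64% |

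The difference between the two factors is 2(1 − ρ) − (1 − ρ²) = (1 − ρ)², which is never negative. ANCOVA is therefore never less precise than raw change. Nor is it less precise than the unadjusted comparison, apart from one error degree of freedom. Raw change is worse than the plain 1-year value whenever ρ is below 0.5. At ρ = 0.5 the unadjusted analysis needs 1/0.75 = 1.33 times the patients that ANCOVA needs.

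**Step 2: what this means in patients.** This uses an exact noncentral-F calculation for four groups, with an assumed Cohen f of 0.25. ANCOVA uses noncentrality divided by (1 − ρ²) and one fewer error degree of freedom. Dropout is handled as n/(1 − 0.2).

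| Analysis | ρ | n per arm | After 20% dropout | Total |
|---|---|---|---|---|
| 1-year value, unadjusted | any | 58 | 73 | 292 |
| ANCOVA | 0.3 | 53 | 67 | 268 |
| ANCOVA | 0.5 | 44 | 55 | 220 |
| ANCOVA | 0.7 | 30 | 38 | 152 |
| Raw change | 0.3 | 81 | 102 | 408 |
| Raw change | 0.5 | 58 | 73 | 292 |
| Raw change | 0.7 | 36 | 45 | 180 |

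Across assumed f of 0.20, 0.25, 0.30 and 0.40, the unadjusted n per arm is 90, 58, 41 and 24. ANCOVA at ρ = 0.5 needs 68, 44, 31 and 18, a ratio of about 0.75 throughout.

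**Step 3: the same result as power.** With 58 analysed per arm and f = 0.25, the unadjusted test has 90% power. At ρ of 0.3, 0.5 and 0.7, ANCOVA has 93%, 97% and 99.7%. Raw change has 77%, 90% and 99%.

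**Step 4: is the first scan a true baseline?** Section 2.1 releases the assignment after registration and entry of baseline data, but does not say that those data include MCE or MPI. Section 2.2.1 admits both patients whose PCI is already done and patients for whom it is only planned. For some patients, then, the immediate scan could follow allocation. It is a safe covariate if it precedes the start of study treatment. If treatment had already begun, adjusting for it could remove part of the effect.

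**The case against.** The strongest reply is that this is a condensed article and its analysis plan is not shown. Covariates and models for repeated measures are commonly left to that plan, and an unadjusted comparison in a randomised trial is valid. This stands in part. It rules out calling the analysis wrong or incomplete. It does not remove the point that the article states a method and a matching sample-size formula, and that both can be improved at no cost while the sample size is still open.

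Several stronger readings are tempting, but the document does not support them:

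- *The analysis ignores the first scan.* Section 2.9 names families of tests to be used as appropriate. A t-test or ANOVA on change from the immediate value is not excluded, and at ρ = 0.7 it would recover 40 of the 49 percentage points.
- *Leaving out the baseline biases the result.* It does not. Chance imbalance is already covered by the standard error of the unadjusted estimate.
- *There is no baseline SAQ, so no SAQ effect can be estimated.* The visit schedule is in Figure 3, which is not shown, and the list of entry data in Section 2.4 is not presented as complete. Even without a baseline, follow-up SAQ scores can be compared between randomised groups.
- *The biomarkers have no baseline.* Table 7 starts them at 1 month, but blood is drawn at entry for biochemical tests, the label Table 7 also uses for this panel. A baseline panel may already be run.
- *The biomarkers will be tested visit by visit.* This is an inference; the text does not exclude repeated-measures ANOVA.

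It is also fair to say that the gain is modest if ρ is low: 4% of the variance at 0.2 and 9% at 0.3.

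**Conclusion.** The concern holds in a limited form. MBF and SDS are measured twice, no named test adjusts for the first measurement, and the text does not say whether the 1-year value or the change is compared. The consequence is lost precision, with validity intact. Relative to the unadjusted 1-year comparison, ANCOVA would cut the variance by 9%, 25% and 49% at assumed correlations of 0.3, 0.5 and 0.7. Raw change would alter it by +40%, 0% and −40%.

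The raw-change figures rest on equal variances at the two times, the ANCOVA figures on a linear relation, and all of them on a correlation that the article does not give. For SDS, if it is skewed and an ordinal model is used, they are a guide only. The patient numbers also rest on an assumed effect size.

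The SAQ point is secondary and conditional on Figure 3. What would be lost is within-patient improvement, not the between-group comparison. Overall this is a change the trial should make, not a defect that undermines it.

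**What to change.** 1. In Section 2.9, state that MBF and SDS at 1 year are compared between groups by ANCOVA with the immediate post-PCI value of the same measure as covariate, using an ordinal model for SDS if it is skewed. This also settles which quantity is analysed. Cost: wording only.
2. First confirm, and state in Section 2.4, that the immediate MCE and MPI are done before study treatment starts in every patient. Cost: a sentence, and possibly a check of local scheduling.
3. Let the pilot estimate the correlation between the two scans and carry it into the sample-size calculation through the factor 1 − ρ². Cost: none beyond the pilot, provided its patients have both scans.
4. Check Figure 3 for a pre-treatment SAQ. If it is there, make Table 7 agree with it. If not, add one SAQ before study treatment and list it in Table 7. Cost: one questionnaire per patient.
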